## Abstract

**Background:**

In malaria endemic areas, schoolchildren usually have asymptomatic malaria infections and consequently remain untreated. Therefore, intermittent preventive treatment with sulfadoxine-pyrimethamine in schoolchildren would be a plausible strategy in malaria stable transmission areas to prevent anaemia and malnutrition. However, in contrast to infancy and pregnancy, antimalaria intermittent preventive treatment in children has been barely investigated. As the implementation of intermittent preventive treatment may be challenged by sulfadoxine-pyrimethamine resistance, sulfadoxine-pyrimethamine combined with piperaquine may be a better alternative than sulfadoxine-pyrimethamine monotherapy. A clinical trial is being conducted to assess the efficacy and safety of intermittent preventive treatments versus controls in Democratic Republic of Congo (DRCongo) schoolchildren and their impact on sulfadoxine-pyrimethamine resistance.

**Methods/Design:**

A phase IIIb, randomised, controlled trial will enroll asymptomatic schoolchildren. For interventions, sulfadoxine-pyrimethamine is compared to sulfadoxine-pyrimethamine plus piperaquine and to a control group. The two treatments are given four-monthly from baseline for a year as a single dose for sulfadoxine-pyrimethamine and two doses at 24-hour intervals for piperaquine. All participants receive praziquantel and albendazole as mass-treatment for helminthiasis at enrolment. The primary endpoint is haemoglobin concentration change at 12 months follow-up. Secondary endpoints are malaria parasite load and malaria prevalence, at baseline and at month 12. Malaria and helminthiasis incidence will be monitored throughout the study. Statistical analysis will use multilevel modelling due to repeated measurements and clustering effect of participants.

**Discussion:**

The very few studies on intermittent preventive treatment in schoolchildren in malaria stable transmission areas have contradictory results. This randomised controlled trial is unique in comparing efficacy and safety of a prophylactic combination therapy to monotherapy or a control group after 12 months follow-up. Resistance markers for sulfadoxine-pyrimethamine (including break through parasitaemias) will also be recorded. Its uniqueness lies also in the fact that we use piperaquine, a long acting antimalarial, in combination with sulfadoxine-pyrimethamine. Artemisinin derivatives have been excluded as it is part of the treatment policies in virtually all malaria endemic countries. Our findings may, therefore, contribute to the public health of youngsters who fail to thrive and grow due to multiple morbidities.

**Trial registration:**

NCT01722539; PACTR201211000449323

## Background

Malaria is a major parasitic disease in developing countries and particularly in Sub Saharan Africa (SSA). Malaria is caused by five plasmodium parasites, the most severe being *Plasmodium falciparum *[1]. More than half of the world population is at risk for malaria. Globally, 243 million clinical malaria cases and slightly more than 1 million deaths are reported annually [2]; 90% of this burden occurs in African children [3,4]. The Democratic Republic of Congo (DRCongo) is likely one of the most affected countries. The malaria transmission is perennial, malaria accounts for 86% of admissions in paediatric emergencies, and the incidence in young Congolese children is estimated at 60 to 100 million malaria attacks per year [5].

Severe anaemia is one of the leading causes of death due to malaria disease in childhood in intense and stable malaria transmission areas [6]. In endemic areas where subjects are permanently exposed to infectious mosquitos bites, severe disease develops in infants and young children. However, in children of five years of age and school-age children, malaria infection is characterised by low recurrent parasitaemia [7]. The prolonged carriage of *Plasmodium* triggers the development of acquired immunity, the premunition that somewhat protects older children and adults against clinical malaria and reduces the risk of death in school-age children [7,8]. Asymptomatic *Plasmodium* infections, if untreated, persist and maintain malaria-induced inflammation that is commonly associated with iron deficiency anaemia through impaired intestinal iron absorption and iron release from hepatocytes, and impairment of the recycling of iron derived from parasitized red blood cells phagocytosis [9]. In low income countries (LICs), more than half of the school-aged population suffers from anaemia; in SSA, approximately 85 million school-aged children are affected. Anaemia reduces their cognitive potential, retards their growth and predisposes them to other diseases [6]. Also malaria accounts about for 13% to 50% of all annual school absenteeism and impairs the educational achievement of children [10].

Intermittent preventive treatment (IPT) with sulfadoxine-pyrimethamine (SP) is a safe and efficacious control tool for malaria that combined or not with insecticidal treated nets, showed substantial protection against malaria in vulnerable populations [11-13]. IPT treats patients at long intervals, permitting drug concentrations to fall below the minimal inhibitory concentration (MIC) between treatment courses. IPT is a public health intervention that builds on clearing existing parasites (treatment effect seen in mass drug administration) to avoid clinical malaria and prevent new infections (prophylactic effect) without affecting the development of immunity. Conversely, in chemoprophylaxis, the blood concentration of the drug is maintained above the level that inhibits the growth of (pre)erythrocytic parasites [14].

IPT markedly reduces clinical malaria incidence and overall child mortality, and improves haemoglobin concentration and the nutritional status of children <5-years-old [12,15]. Additionally, IPT may decrease malaria transmission amongst the most vulnerable individuals through a post-treatment prophylactic effect [14]. IPT is delivered through antenatal consultations for pregnant (IPTp) women and through vaccination programs for infants (IPTi). A policy recommendation has been developed by the World Health Organization for IPTp and IPTi [4,16,17]. Schools have been suggested as possible delivery sites for IPT in children (IPTc). Indeed, the education sector may represent a reliable system for malaria control. IPT in schoolchildren (IPTsc) is likely the most feasible and appropriate chemoprevention in stable and endemic areas because schoolchildren are usually asymptomatic to malaria infection and are consequently untreated in practice. Therefore, if proven effective, IPTsc would be of direct benefit for the schoolchild, contribute to malaria control at school, and facilitate on a community-wide basis the implementation of other control interventions, that is, vector control, IPTi, and malaria primary diagnosis and treatment [18].

Favourable drugs for use as IPT should balance long half-life against efficacy, safety, tolerability and potentiality for cross-resistance selection [16]. Use of long-acting drugs would result in fewer intakes and higher treatment compliance. SP is an established product in the treatment of IPTp. The drug has further proven safety and tolerability in children in clinical trials. SP is slowly eliminated and provides 60-day antimalaria protection for fully sensitive *P. falciparum*.

Other long-acting drugs available are mefloquine, amodiaquine, and piperaquine. However, due to safety concerns, mefloquine might not be optimal for IPT. Amodiaquine is not suitable for IPT due to its three-day treatment regimen and is used as a first line treatment in several countries including DRCongo. Piperaquine has been extensively used for mass prophylaxis and treatment since 1978 in China and other malaria endemic countries of Asia [19]. Piperaquine has a long half-live and may be a good IPT candidate in malaria endemic countries [20].

Pyrimethamine binds to dihydrofolate reductase (DHFR) enzyme and sulfadoxine to dihydropteroate synthase (DHPS) and, thereby, the two SP components inhibit the *P. falciparum* life cycle [21]. However, SP resistance has spread globally due to *pf*DHFR and *pf*DHPS gene mutations as a consequence of an increasing proportion of individuals unnecessarily exposed to drugs [22]. Of note, antimalarials with lengthy elimination half-lives have a higher propensity of selecting for resistance due to exposure of new infecting malaria parasites to the drug when its concentration tail falls below the MIC [23].

To minimise the risk of SP resistance, SP could be combined with piperaquine (SP-PQ) as recommended by Cairns *et al.* and Gready [20,24]. Also, SP and SP-PQ, given at four-month intervals in line with the long half-lives (around 20 days) in paediatric patients, may improve treatment compliance. Nevertheless, evidence about the efficacy and safety of IPT SP and SP-PQ in the presence of SP resistance strains selection is not yet substantiated in schoolchildren. Only three clinical trials with restricted treatment arms and/or follow-up have so far been performed on IPTsc in hyper endemic areas. Further clinical trials are warranted in other settings. Through a randomised controlled trial (RCT) we will assess the efficacy and safety of IPT SP or SP-PQ regimens versus controls in schoolchildren of the DRCongo.

### Study hypothesis

Considering the facts that in our study area: (1) IPT of malaria provides substantial protection against anaemia and malaria in school children; (2) the level of SP resistance has no significant impact on the prophylactic efficacy [25]; and (3) SP-PQ is safe and as efficacious as SP, we hypothesize that antimalarial IPT with SP and SP-PQ will improve haemoglobin concentration, reduce anaemia prevalence, malaria incidence and parasitaemia, and improve nutritional status and school performance in school-aged children of DRCongo.

## Methods/Design

### Trial objectives and purpose

#### *Primary objectives*

This study primarily aims to assess the effect of antimalarial IPT on anaemia one year after initial intervention in school-aged children of stable malaria transmission and hyper endemic areas.

#### *Secondary objectives*

Secondarily, in the same study population, the purpose of the study is to:

1. Determine the prevalence of SP resistance markers at baseline and at month 12 follow-up;.

2. Compare the efficacy and safety of SP versus SP-PQ.

3. Assess the impact of antimalarial IPTsc on malaria incidence and severity.

4. Evaluate the impact of IPTsc on the nutritional status of schoolchildren.

5. Evaluate the effect of antimalarial IPTsc on school performance.

6. Identify the potential environmental and host-related predictors of malaria (re)infections.

### Study design

#### *Study area*

The study is conducted in the Mokali health area of the Biyela health zone, in Kinshasa province. The health zone of Biyela has recently been identified as highly endemic for malaria and prevalent for schistosomiasis and soil transmitted helminths (STH) (unpublished observations of [name]). Biyela is urban–rural and its population is estimated at 182,421 inhabitants. Biyela has nine subzones of which two are considered rural. Three rivers cross the health zone: Mango, Mabanga and Mokali. Of the nine health areas of Biyela, Mokali is the most populous with a population estimated at 27,455 inhabitants. Biyela has one regional reference hospital that is located in the Mokali health area. The participants in the study are recruited at EP Boyambi and EP Likabo, two of the nearest primary schools of Mokali to the regional health centre. EP Boyambi and EP Likabo were built by the Catholic Church and each school has 14 teachers and 12 classes (two classes per each school year). The estimated number of schoolchildren was 650 per school at the beginning of the year.

### Patient selection and withdrawal

#### *Inclusion criteria for initial treatment*

In order to be eligible, children should satisfy all of the following criteria:

1. Male and female primary school children.

2. Anticipated local residence for the study duration.

3. Signed or thumb-printed informed consent by the parents or guardians and witnessed by an impartial witness (whenever parents/guardians are illiterate).

4. Informed consent for children 12-years-old or older.

#### *Exclusion criteria*

Participants with at least one of the following criteria are excluded:

1. Children of the sixth primary school year.

2. Participation in any other investigational drug study (antimalarial or others) during the previous 30 days.

3. Known or suspected hypersensitivity or serious adverse events (AE) to the study drugs.

4. Malaria symptoms at baseline irrespective of the severity [see Additional file 1].

5. Febrile conditions caused by diseases other than malaria at the first visit.

6. Decompensated anaemia.

7. Illness or conditions, such as hematologic, cardiac, renal, hepatic diseases, which in the judgement of the investigators would place the subject at undue risk or interfere with the results of the study, including known glucose-6-phosphate dehydrogenase deficiency and sickle cell.

8. Body weight <14 kg.

9. Children with major chronic infectious diseases (HIV, tuberculosis, and so on).

#### *Withdrawal criteria*

Patients will be excluded from further assessment if any of the following criteria are met:

1. Withdrawal of informed consent.

2. Severe AE related to the study drug.

3. Termination of the study prior to its planned end date by the sponsor, regulatory authorities, or Ethics Committee.

Every reasonable effort is made to complete a final evaluation of participants who are withdrawn from the study prior to the planned termination time period. The study staff records the reason(s) for all withdrawals from the study in the participants’ study records. At the time of withdrawal, all study procedures outlined for the End of Study visit should be completed. Any withdrawal or loss to follow-up are documented and notified to the site coordinator as soon as possible.

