### Design and sample size calculation

The study is an unblinded, randomised controlled trial, enrolling asymptomatic school children, either gender. At baseline, month four, and month eight, IPT with SP or SP-PQ is given. SP is administered as a single treatment dose. However, PQ is given as two doses with a 24-hour interval. IPT is administered at four month intervals in line with the long half-lives of the drugs and for compliance. Each treatment arm will be compared to the control group of untreated participants. Due to the prevalence of STH and schistosomiasis in the study area all participants are treated with albendazole or praziquantel according to the WHO guidelines [26]. Before the study, parents or guardians and children were informed about the objectives and the design of the study during organised meetings at schools.

Within each school, each schoolchild is randomly assigned to one of the two intervention groups or the control group as follows: IPT-SP, IPT-SP-PQ and no-treatment. Each study arm consists of one-third of all individuals.

To estimate the statistical power of our studies, we used an effect size of 0.56 g/dl mean Hb level improvement by the antimalarial IPT compared to the control treatment. This effect size was based upon a previous study.

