### Statistical analysis plan

The effect of the type of intervention (either IPT versus the controls, or SP versus SP-P) will all be analysed using linear mixed model analysis. In each analysis, Hb concentration is modeled versus time, testing whether the change of Hb concentration over time differs between the two types of intervention. In each case, a linear mixed model is fitted with Hb concentration as outcome variable, and fixed effects including the type of intervention (indicator variable), time and the interaction between them. In these models, the effect of interest is the interaction between intervention and time, which formally tests the null hypothesis that the change in Hb concentration with time is the same in all interventions. Significance of the interaction term is tested using the F-test with a Kenwardroger correction for the number of degrees of freedom. As the study includes several (longitudinal) measurements within the same individual, and since the individuals cluster within schools, the dependency between individuals will be accounted for by including random effect terms into the model. More particularly, the model will include random effects (intercept and slope) for individual, nested within the random effect of school. An additional advantage of this technique is that it gives unbiased results in case individuals are lost to follow-up during the study.

Analysis of the data will be performed using the nlme package from the statistical software R or the proc mixed procedure from the software package SAS. All statistical analyses will be performed in close collaboration with StatUa, the Center for Statistics at the University of Antwerp.

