### Medicines accountability procedures

The study site maintains the study drugs under adequate security. Study drugs sent to the study centre are verified by the investigator or designee; the amount sent and the exact supplies received are documented by signing and dating the appropriate shipping documents. Study drugs are dispensed as per the randomization list to each patient who meets the enrolment criteria. The investigators or designees record the patient’s number, patient’s initials and date dispensed on the Drug Accountability Form. The investigators maintain an accurate running accountability of the study drugs. At the end of the study, final disposal of the unused drugs will be decided by the sponsor after final reconciliation has been made.

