### Treatment administration

The study treatment is administered under the direct supervision of a study nurse. Study drugs are given to the children consistent with the investigational brochure of each product. After drug administration, children will be kept for thirty minutes in the class. In case vomiting occurs within 30 minutes of administration a dose is repeated in full. This event is documented in the CRF. If vomiting persists beyond two additional doses, the child is withdrawn from the study.

Upon arrival at a school, an inventory is performed and a drug receipt log filled out and signed by the staff. Accountability for the drug at all school sites is the responsibility of the principal investigator. The investigators ensure that the drug is used only in accordance with this protocol. Accountability records include dates, quantities, lot numbers, expiration dates, and patient numbers.

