### Ethical considerations

The Investigators agreed to conduct the present study in full agreement with the principles of the 'Declaration of Helsinki’ and subsequent relevant amendments. All research activities will be conducted in accordance with the standards and codes of conduct accepted by the ICH guidelines. The study is approved by the Ethical Committees of the University of Antwerp, Belgium and of the School of Public Health, University of Kinshasa, DRCongo. Approval was also obtained from the Ministry of Health of DRCongo. Prior to the start of the project, special permission was obtained from the DRCongo Ministry of Education and the local health and education authorities of Biyela. Written informed consent was obtained from the guardians for all children before entering the study. An assent was obtained, as well, from children who were 12-years-old or older. In the control arm no treatment is given as no foreseeable serious risk can be anticipated and no standard of care yet exists in schoolchildren. All participants are followed-up, examined and treated free of charge if malaria or other illnesses occur during the period of the study.

To measure Hb level and *P. falciparum* parasitaemia, finger pricks are done at each visit for hemocontrol and microscopy. A total of 3 ml of venous blood is collected at baseline and month 12 for genotyping and other tests that the clinician may request for the management of illnesses. Residual plasma is separated, stored and transported at -70°C to be assayed by ELISA and fluorescence activated cell sorting (FACS) for malarial cytokines and antibody quantification and other malaria-related parameters (described in an independent protocol after the operational part of the study is finished). The human genome will not be examined.

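### Drug-related withdrawal ends Hb assessment as well as dosing, so month-12 data can go missing by arm, and the claim that the mixed model is unbiased under loss to follow-up lacks its condition

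*Protocol article*

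**What the plan says.** **Who leaves, and what ends.** Under Withdrawal criteria: "Patients will be excluded from further assessment if any of the following criteria are met". The three criteria are withdrawn consent, "Severe AE related to the study drug", and early termination of the study. The same section asks for the End of Study procedures to be completed when the child is withdrawn.

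**A further trigger elsewhere.** Treatment administration says: "If vomiting persists beyond two additional doses, the child is withdrawn from the study". This is withdrawal from the study, not only from the drug, and it is not in the Withdrawal criteria list.

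**Who can meet these rules.** Design and sample size calculation: "The study is an unblinded, randomised controlled trial" and "Each treatment arm will be compared to the control group of untreated participants". Ethical considerations: "In the control arm no treatment is given as no foreseeable serious risk can be anticipated". Medicines accountability procedures: "Study drugs are dispensed as per the randomization list to each patient who meets the enrolment criteria".

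**What is to be estimated.** The primary endpoint is the change in mean Hb at month 12, together with anaemia prevalence at one year.

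**The claim about missing data.** The Statistical analysis plan section describes a linear mixed model of Hb over time and adds that "it gives unbiased results in case individuals are lost to follow-up during the study". It attaches no condition.

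**The concern.** Two separate decisions are merged: stopping the study drug and leaving the study. A child who reacts badly to the drug also stops contributing Hb at the remaining visits. On the natural reading of study drug, this can happen only in the SP and SP-PQ arms, so the loss of primary-endpoint data is tied to allocation by rule. The two active arms may also differ, since piperaquine is given as two doses a day apart and SP as one. Whether an event is drug-related is a clinical judgement made in an unblinded trial.

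The evaluation at withdrawal gives an Hb value at that time, not at month 12. The vomiting rule shows the gap most clearly. It operates around dosing, so a child withdrawn at the first round yields in effect a second baseline value and no later Hb. Anaemia status at one year is also lost, and a linear model of Hb does not itself supply it.

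The unbiasedness sentence then presents loss to follow-up as harmless. Month-12 values that are never collected cannot be recovered at analysis.

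**Working it through.** **1. The plan's own figures.**
- Effect size: 13.01 − 12.45 = 0.56 g/dl, as stated.
- Sample size: (1,300 − 200) × (1 − 0.20) × (1 − 0.30) = 616, as stated. With 40% absenteeism it would be 528.
- Per arm: 616 / 3 ≈ 205. So 1%, 5% and 10% of an arm are about 2, 10 and 21 children.
- The difference quoted for SP versus SP-PQ is 0.27 g/dl.
- No drug-related withdrawal rate is given, and nothing is said about later Hb in withdrawn children. Both are assumptions below.

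**2. Bias formula.** Let *p* be the fraction of an active arm withdrawn. Let *g* be the amount by which their unobserved month-12 Hb falls below the model's prediction *m*. The mean over all randomised children in that arm is (1 − *p*)*m* + *p*(*m* − *g*) = *m* − *pg*. The model reports *m*, so the bias is *p* × *g*.

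**3. Active arm versus control**, with no such withdrawals in control:

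| Withdrawn | *g* = 0.56 (whole benefit lost) | *g* = 1.0 (assumed) |
|---|---|---|
| 1% | 0.006 | 0.01 |
| 5% | 0.028 | 0.05 |
| 10% | 0.056 | 0.10 |

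Bias is in g/dl. Relative to 0.56, the first column is 1%, 5% and 10%. The second is 1.8%, 8.9% and 17.9%.

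**4. SP versus SP-PQ.** Both arms are subject to the rules, so only the difference counts: bias = *p*₁*g*₁ − *p*₂*g*₂. With 5% versus 3% withdrawn and *g* = 1.0 in both, (0.05 − 0.03) × 1.0 = 0.02 g/dl, and 0.02 / 0.27 = 7%.

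**5. When is the mixed model unbiased?** A simulation used visits at months 0, 4, 8 and 12, a true effect of 0.56, and assumed between- and within-child SDs of 1.0 and 0.8. Withdrawals occurred after month 4 in the active arm only. The fitted model had a random intercept and treated visits as categories, which is simpler than the plan's model. Bias is measured against the effect with complete data; the ± figure is Monte Carlo error.

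| Reason for withdrawal | 5% withdrawn | 10% withdrawn |
|---|---|---|
| Random within the arm | 0.001 ± 0.002 | −0.004 ± 0.003 |
| Driven by Hb already observed | 0.000 ± 0.001 | −0.001 ± 0.002 |
| Unobserved fall reaching 1.0 g/dl by month 12 | +0.051 ± 0.004 | +0.094 ± 0.003 |

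The first two rows are missing at random and show essentially no bias, although all withdrawals are in one arm. The third is not missing at random, and its bias is close to *p* × *g*. The model's protection therefore depends on a condition that the sentence leaves out.

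**The case against.** **The size is probably small.** The article describes SP as safe and well tolerated in children, and the vomiting rule applies only after two further doses have failed. Nothing suggests that 5% to 10% would leave this way. The allowance for cancelation and absenteeism is far larger. A 1.0 g/dl gap is nearly twice the planned benefit and has no support in the document. This stands, which is why the 0.56 column comes first.

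**Unequal withdrawal is not bias.** This also stands, as the simulation shows. A reader might infer that the comparison is no longer as randomised, or that the rule favours IPT. The document supports neither. It ends further assessment but nowhere says that withdrawn children leave the analysis, and their earlier values and the value at withdrawal can enter the model. The direction favours IPT only if these children later do worse than predicted.

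**The non-inferiority figure.** A reader might set 0.05 or 0.10 g/dl directly against 0.27 and get 19% or 37%. That assumes no such withdrawals in the other active arm, which is subject to the same rules.

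**Controls could qualify.** Albendazole and praziquantel go to all children and appear, as non-investigational products, under the Study drugs heading. If they count as study drug, a control child could meet the adverse event criterion. The accountability section's wording makes the narrower meaning more natural, but the text is not explicit.

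**Later harms.** A reader might infer that harms after withdrawal go unrecorded. Health centre visit, Safety assessment and Ethical considerations provide for recording hospital attendances, the outcome of each event, and free care during the study. What is lost is adverse event collection at the scheduled visits.

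**Analysis detail.** Sensitivity analyses for missing data are commonly left to a statistical analysis plan, so their absence here is no finding. The unbiasedness sentence differs: the article makes that statement, and it needs correcting.

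**Conclusion.** The point holds in limited form. As written, the plan stops collecting primary-endpoint data under rules that, if study drug means the randomised products, only the two active arms can meet. The evaluation at withdrawal does not fill the gap. The unconditional statement about unbiased results is wrong as stated, and the two sections on withdrawal do not match.

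The size is unknown and likely modest. Against control it is 0.028 g/dl at 5% withdrawn if the whole benefit is lost, and 0.05 g/dl under an assumed 1.0 g/dl gap. For SP versus SP-PQ only the difference between those arms matters, about 0.02 g/dl in the example. These figures assume that the model predicts withdrawn children as if they had continued. If their later Hb matches that prediction, the bias is nil; if it is better, the sign reverses. The change is still worthwhile because the data cannot be recovered afterwards and the article gives the trial status as recruiting.

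**What to change.** - **Separate stopping drug from leaving the study.** Leave the drug-stopping rules as they are. Unless consent is withdrawn or the study is terminated, continue Hb, smear and adverse event assessment at the remaining scheduled visits to month 12, and analyse the child in the assigned arm.
- **Correct the claim.** In the Statistical analysis plan section, replace the statement of unbiased results with one saying that the results are valid if data are missing at random given the data in the model.
- **Reconcile the two passages.** Withdrawal criteria and Treatment administration should give the same list of triggers and say whether each one ends drug, assessment or both. State whether study drug covers only the randomised products.

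The cost is a wording change. A few children keep finger pricks at visits already scheduled at their schools.
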